### Sample size calculation

We assumed MICT is superior to guideline-based group in glucose control and cognitive function. Moreover, we also test whether HIIT was superior to MICT group. Limited studies have compared the HIIT or MICT and guideline groups on HbA1c or BDNF. We assumed a glycosylated hemoglobin (HbA1c) mean (SD) difference in change of 0.2 (0.3)% between MICT groups and guideline groups. Based on previous study (Terada et al., 2013), an additional mean (SD) difference in change of HbA1c of 0.2 (0.3)% between HIIT and MICT was assumed. The mean difference (SD) in BDNF levels was assumed to be 1.2 (1.4) ng/ml between MICT and guideline group. Additional 1.2 (1.4) ng/ml for BDNF between HIIT and MICT was assigned (Kovacevic et al., 2020). We will adopt the larger sample size to ensure adequate power. Finally, we intend to enroll 330 participants (110 per group) with a power of 90%, a one-sided α of 0.025 and an expected dropout rate of 20%. The α value of 0.025 will be equal assigned to HbA1c and BDNF. PASS software (version 15.0, NCSS Statistical Software) was used to calculate sample size. If the upper confidence interval of the MD in HbA1c levels between the HIIT or MICT interventions and the reference group falls below zero (<0.0%), HIIT or MICT is considered superior to the reference group in terms of improving glucose control. When the lower confidence interval > 0.0% of the MD in BDNF, it would be declared superior to the reference group for improving cognitive function.

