### Primary outcomes

#### Glycosylated hemoglobin

To measure HbA1c levels, venous blood samples will be collected in the morning from participants in a fasting state, both before and after the 12-week intervention period. The blood samples will be gently mixed by inverting them multiple times and then allowed to stand at room temperature for 2 h. Afterward, the samples will be centrifuged at 3,000 rpm for 5 min at 4°C. The determination of HbA1c content will be conducted using a fully automated HbA1c analyzer through high-performance liquid chromatography. Each index will be recorded twice to ensure accuracy, and the average value of the two measurements will be used for statistical analysis. In this study, a HbA1c change of 0.2% will be considered the minimum effect size that would have clinical significance and would be of interest in comparisons between the HIIT or MICT groups and the guideline group. HbA1c is an excellent indicator for long-term blood glucose level for 3 months.

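### The stated sample size inputs do not reproduce 330 participants at 90% power, on either reading of the SD

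*Protocol article*

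**What the plan says.** All of the inputs stand in one paragraph, Sample size calculation:

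- HbA1c, MICT against guideline: "mean (SD) difference in change of 0.2 (0.3)% between MICT groups and guideline groups".
- HbA1c, HIIT against MICT: "an additional mean (SD) difference in change of HbA1c of 0.2 (0.3)% between HIIT and MICT was assumed".
- BDNF, MICT against guideline: "The mean difference (SD) in BDNF levels was assumed to be 1.2 (1.4) ng/ml between MICT and guideline group".
- BDNF, HIIT against MICT: "Additional 1.2 (1.4) ng/ml for BDNF between HIIT and MICT was assigned".
- Choice between the two outcomes: "We will adopt the larger sample size to ensure adequate power".
- Result: "enroll 330 participants (110 per group) with a power of 90%, a one-sided α of 0.025 and an expected dropout rate of 20" percent.
- Multiplicity: "The α value of 0.025 will be equal assigned to HbA1c and BDNF".

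Superiority is judged by a confidence limit against zero, so no margin enters the calculation. The paragraph names the software (PASS 15.0). It gives no further division of α over comparisons, no joint-power target and no other reason for a larger number.

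**The concern.** The article does not leave this calculation to another document. It publishes effect, SD, α, power, dropout and result, so the inputs should lead to the result. They miss it by a wide margin: on the natural reading 330 is about 50% more than they require (330/219 = 1.51).

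What is at stake is whether the stated power can be trusted. Either an input is misreported or an adjustment was made that the text does not mention. A reader cannot tell which, and the possibilities point in opposite directions: the trial may have clearly more than 90% power for HbA1c, or less.

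**Working it through.** **Inputs** (all from Sample size calculation). HbA1c: δ = 0.2, SD = 0.3, so d = 0.667. BDNF: δ = 1.2, SD = 1.4, so d = 0.857. The values are the same for both adjacent contrasts. Power is 90% (z = 1.2816) and dropout 20%. One-sided α is 0.025, or 0.0125 per outcome after the equal split (z = 1.9600 or 2.2414).

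**Formula.** Evaluable per arm: n = 2(z₁₋α + z₁₋β)²/d². Enrolled per arm: n/(1 − 0.20), rounded up. The noncentral t result is given beside the normal one.

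**Attempt to reproduce the plan's figure.** 110 enrolled per arm leaves 110 × 0.8 = 88 evaluable, so a 90% power calculation should return about 88.

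*Natural reading: 0.3 is the per-arm SD of change, α = 0.0125.*
- HbA1c: 2 × (2.2414 + 1.2816)²/0.667² = 55.9, so 56 (t: 58). Enrolled: 56/0.8 = 70 and 58/0.8 = 72.5, so 73. Total 210–219.
- BDNF: 2 × (3.5230)²/0.857² = 33.8, so 34 (t: 36). Enrolled 43–45 per arm. Total 129–135.
- HbA1c is the larger, so the plan's own rule gives 210–219.

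*Other readings tried, HbA1c, 90% power:*

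| Reading | Evaluable per arm (z / t) | Enrolled per arm | Total |
|---|---|---|---|
| α 0.025, not split | 48 / 49 | 60 / 62 | 180 / 186 |
| α 0.0125 | 56 / 58 | 70 / 73 | 210 / 219 |
| α 0.00625 (also split over two contrasts) | 65 / 66 | 82 / 83 | 246 / 249 |
| α 0.025/6 | 70 / 71 | 88 / 89 | 264 / 267 |
| SD 0.3√2 = 0.424, α 0.025 | 95 / 96 | 119 / 120 | 357 / 360 |
| SD 0.424, α 0.0125 | 112 / 113 | 140 / 142 | 420 / 426 |

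By simulation, about 90% joint power for all four tests at 0.0125 needs about 70 evaluable per arm, or about 264 in total. None of these gives 330. It is reached only by adding inputs that the text does not state, for example one-sided α of 0.003125 with about 95% power.

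**Power at 88 evaluable per arm** (noncentral t):

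| SD used | α 0.0125 | α 0.025 |
|---|---|---|
| HbA1c, 0.3 | 98.4% | 99.3% |
| HbA1c, 0.3√2 | 80.6% | 87.5% |
| BDNF, 1.4 | above 99.9% | above 99.9% |

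Check by the normal formula for the first cell: 0.667 × √(88/2) = 4.422; 4.422 − 2.241 = 2.181; Φ(2.181) = 98.5%.

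**Tolerance.** At α = 0.0125 and 88 per arm, power for a 0.2% difference stays at 90% up to an SD of change of 0.374 (t) or 0.377 (normal), so about 0.37.

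**The case against.** The best defence is that the error is harmless: on the natural reading the trial has more than the promised power, and a condensed article may omit a contrast or joint-power adjustment. Part of this stands. Over-enrolment would not invalidate the trial, and an allowance for uncertainty could be legitimate. But the paragraph claims no such allowance; it ties 330 directly to 90%. The two obvious adjustments, a further split of α and joint power, still stop at about 250–267.

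A reader might go further than the documents allow in two ways.

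- *That the trial is overpowered and enrols about 110 older participants without need.* The figure is 330 − 219 = 111, and it holds only if 0.3 is the per-arm SD of change. The article attaches the SD to a difference in change and does not say whose SD it is. With the √2 factor the trial is short of participants. On that reading 80% power at 0.0125 would need 87 evaluable, or 109 enrolled per arm, close to the stated 110. This is conjecture and contradicts the stated 90%, so it does not rescue the paragraph, but it shows that the direction of the error is open.
- *That the size lets trivial effects be declared superior.* The HbA1c outcome section says "a HbA1c change of 0.2% will be considered the minimum effect size that would have clinical significance", while 88 per arm can declare superiority at an observed difference of about 0.10%. This does not follow from the error. Any test against zero sized at 90% for 0.2% succeeds from 2.2414/(2.2414 + 1.2816) = 0.64 of that effect, so from about 0.13% even at the smaller size. The article does not make 0.2% a success margin.

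**Conclusion.** The point holds as a failure to reproduce: the published inputs and the published size cannot both be right at 90% power. On the natural reading the inputs call for 210–219 participants (180–186 with α unsplit), and 88 evaluable per arm gives about 98% power for HbA1c. With the √2 reading they call for about 360–426, and the power is about 81–87%. Which branch applies is not established, so neither overpowering nor a surplus of about 110 participants can be asserted without that condition. The figures assume a two-sample comparison of mean changes with equal arms, a common SD and exactly 20% dropout. The correction should be made, but it does not threaten the design.

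**What to change.** Keep enrolment at 330 and correct the paragraph in this order:

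1. Recover the inputs entered in the software: whose SD the 0.3 and 1.4 are (per-arm SD of change, or another quantity), α per test, power, and any adjustment for the number of contrasts.
2. State those inputs in Sample size calculation.
3. Restate the power that 110 per arm (88 evaluable) delivers with them, for each primary outcome.

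If the published inputs prove to be the real ones, suitable wording is: *With 110 per arm (88 evaluable after 20% dropout), one-sided α of 0.0125 per outcome and a per-arm SD of change of 0.3%, power to detect an HbA1c difference of 0.2% is about 98%; it remains at 90% for an SD of change up to about 0.37%.* This sentence should not be adopted before step 1, because it would be false if the SD was something else.

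The cost is one paragraph and a look at the saved calculation. Recruitment and conduct do not change.

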### Measurements

The research assistants who blinded to group allocation will collect baseline data from the patients, including age, course of the disease, height, weight, blood pressure, smoking history, socioeconomic status, time since retirement, and history of antidiabetic medication. These assessments will provide a comprehensive overview of the participants’ characteristics. The primary outcome measures of the study will be the HbA1c and BDNF levels. Additionally, the secondary outcome measures will include physical activity levels, anthropometric parameters (weight, waist circumference, hip circumference, and BMI), physical parameters (including fat percentage, muscle percentage, and the fitness rate), cardiorespiratory fitness indicators (blood pressure, the heart rate, vital capacity, and maximum oxygen consumption), biochemical indicators (high-density lipoprotein, low-density lipoprotein, triglyceride, total cholesterol, and HbA1c), inflammation level (C-reactive protein), cognitive function (assessed through reaction time and dual-task gait test performance), and motor function (evaluated through static balance, dynamic balance, single-task gait test performance, and grip strength). To collect these data, participants will be assessed before the start of the intervention and again after the 12-week intervention. Notably, all exercise tests and data collection will be conducted by research assistants blinded to patient group allocation.

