### Brain-derived neurotrophic factor

Fasting participants will provide blood samples before and after the 12-week exercise intervention to measure serum BDNF levels. The analysis of serum BDNF levels will be performed using an enzyme-linked immunosorbent assay (ELISA) kit in accordance with the instructions provided by the manufacturer. BDNF is considered an indicator of neuroplasticity and cognitive function, and decreased BDNF levels have been associated with cognitive (Zhen et al., 2013).

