### Statistical analysis

The intention-to-treat principle will be employed for all analyses, ensuring that participants are analyzed according to their assigned treatment groups. Linear mixed models will be utilized, incorporating participant and baseline values as random effects, to estimate changes within groups (with a difference between groups of *P* < 0.1) for all outcome measures. To address missing data, the multiple-imputation method will be employed to test its influence on the analysis. All statistical analyses will be conducted using R software (version 4.0.2, the R Project for Statistical Computing^2^). The hypothesis tests will be two-sided, and statistical significance will be defined as *p* < 0.05. For the primary outcomes, multiple will be not necessary as the α value have been allocation in the sample calculation. Importantly, no adjustments for multiple comparisons will be made for secondary outcomes, and therefore, their interpretation should be considered exploratory in nature. Subgroup analyses based on sex, duration of T2DM, and BMI will also be performed to examine potential variations within these subgroups. A per-protocol sensitivity analysis will be applied.

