Current evidence regarding HIIT-induced improvements in motor function primarily comes from skeletal muscle adaptations, while conclusions regarding overall motor function in older patients with T2DM are lacking. Sedentary elderly patients with T2DM exhibit worse muscle function and have a higher risk of falls (due to slower gait speed and poor balance control). Therefore, we evaluated the effects of HIIT and MICT on muscle strength and overall movement (dynamic and static balance and gait) in sedentary elderly patients with T2DM.

To date, the specific effects of HIIT and MICT on cognitive function in elderly sedentary patients with T2DM remain unknown. Most studies investigating the impact of HIIT on cognitive function have been conducted in healthy older individuals or animal models. These studies have revealed divergent effects of HIIT and MICT on different aspects of cognitive function. Regarding overall cognitive function, MICT has been reported to provide the greatest benefit in terms of executive function, whereas HIIT has yields greater improvements in information processing speed (Coetsee and Terblanche, 2017). Importantly, cognitive impairment in patients with T2DM manifest in a variety of ways, including reduced levels of cognitive markers such as BDNF, decreased information processing speed, and impaired performance during the dual-task gait test (Silsupadol et al., 2009; Kovacevic et al., 2020; Novak et al., 2022). Given these considerations, we evaluated the effects of HIIT and MICT on elderly sedentary patients with T2DM from multiple perspectives, including cognitive markers, information processing speed (reaction times), and movement-cognition interaction (the dual-task gait test).

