This trial is subject to several limitations that should be acknowledged. First, this study will not include an in-depth analysis of metabolic marker alterations in response to exercise in patients with T2DM. Future research could incorporate metabolomics to investigate changes in cardiovascular markers in response to exercise. Second, we will not conduct a comprehensive investigation into motor and cognitive functions. Future studies could employ neuroimaging tools to assess changes in cognitive-related cortical activity and functional connectivity. Additionally, improving the detection accuracy is crucial. Assessment of dynamic cortical activity data during exercise could provide valuable insights into the cortical mechanisms underlying changes in motor function, and muscle strength testing could be enhanced through the use of objective equipment such as isokinetic devices. Furthermore, the study population will consist of only Asian individuals. Racial and regional differences may limit the generalizability of the findings.

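### The decision rule confirms better cognitive function from serum BDNF alone, while the protocol's own cognitive tests stay exploratory

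*Protocol article*

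**What the plan says.** All references are to the protocol article.

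- **Primary outcomes (Measurements).** "The primary outcome measures of the study will be the HbA1c and BDNF levels".
- **Decision rule (Sample size calculation).** When the lower confidence limit of the BDNF difference lies above zero, "it would be declared superior to the reference group for improving cognitive function". The section opens by framing the hypothesis in the same terms: MICT is expected to beat the guideline programme on glycaemic control and on cognition.
- **Secondary outcomes (Abstract, Measurements).** The list includes "cognitive function (assessed through reaction time and dual-task gait test performance", separately from BDNF.
- **Status of secondary outcomes (Statistical analysis).** "no adjustments for multiple comparisons will be made for secondary outcomes, and therefore, their interpretation should be considered exploratory in nature".
- **Reason for using BDNF (Brain-derived neurotrophic factor).** "BDNF is considered an indicator of neuroplasticity and cognitive function". The section adds that lower levels have been associated with cognition.

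**The concern.** One term carries two meanings with different evidential status. In the decision rule, cognitive function is something that a blood assay can confirm. In the outcome list it is something measured by performance tests, and those results are exploratory. No section reconciles the two.

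A decision rule written in advance fixes the sentence that the trial is entitled to publish as confirmed. Here that sentence is about function, but the evidence behind it is a serum protein. The Conclusion section wants the results to guide exercise prescriptions for older sedentary patients, so readers could take a confirmed cognitive benefit at face value even if the trial's own cognitive tests gave no support.

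**Working it through.** No arithmetic decides this point. It turns on what the rule requires, what the protocol means by cognitive function, and what the protocol offers to link the two.

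**1. What the rule requires.** It has one condition: the lower confidence limit for the BDNF difference is above zero. Reaction time and dual-task gait do not enter it.

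**2. What the protocol means by cognitive function.** The Abstract and Measurements sections both attach the term to reaction time and dual-task gait. Both list BDNF apart from it, as a primary outcome.

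**3. What links BDNF to cognition.** The BDNF section calls it an indicator and cites an association with lower levels. The Discussion counts reduced BDNF among the ways in which cognitive impairment shows itself in type 2 diabetes. It then names three perspectives: cognitive markers, processing speed (reaction time), and the interaction of movement and cognition (dual-task gait). BDNF is therefore one view among three. No section says that a rise in BDNF produced by exercise implies better cognitive performance.

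**4. Whether one marker can stand for the whole.** The Discussion reports of earlier work, mostly in healthy older people or animals: "These studies have revealed divergent effects of HIIT and MICT on different aspects of cognitive function". It gives MICT the advantage for executive function and HIIT for processing speed. On that account, a single BDNF difference between HIIT and MICT cannot say which regimen is better for cognition in general.

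**5. What the rule yields in each case.**

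| BDNF lower limit | Reaction time and dual-task gait | Declaration under the rule |
|---|---|---|
| Above 0 | Better | Superior for cognitive function |
| Above 0 | No difference | Superior for cognitive function |
| Above 0 | Worse | Superior for cognitive function |
| Not above 0 | Better | None |

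In the second and third rows the confirmed statement has no support from the tests that the protocol uses to assess cognitive function, or runs against them. In the fourth row the tests favour the intervention and nothing is declared.

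**6. The unit.** The rule writes the BDNF threshold as a percentage, although the same section plans BDNF in ng/ml: "The mean difference (SD) in BDNF levels was assumed to be 1.2 (1.4) ng/ml between MICT and guideline group". A difference of zero is the same in either unit, so no decision changes. This is a clerical correction only.

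**The case against.** The strongest reply is that the protocol is open about treating BDNF as a cognitive measure. It calls BDNF an indicator of cognitive function, groups it with the cognitive markers, and uses parallel shorthand for the other primary outcome, where HbA1c stands for glucose control. The cognitive tests are prespecified and CONSORT reporting is promised, so readers should see them beside the BDNF result.

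Much of this stands. It justifies BDNF as a biomarker endpoint and makes concealment of the test results unlikely. It does not justify the wording of the declaration. The HbA1c parallel is also imperfect: the protocol describes HbA1c as reflecting blood glucose over about three months, which is close to the thing being claimed, whereas it measures cognitive function by other tests.

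A reader might infer four stronger points, which the documents do not support:

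- **BDNF is an invalid surrogate or the wrong primary outcome.** The documents contain no evidence that it fails, and the source cited for it is not available here.
- **The rule is too easily met.** Assume 88 completers per arm (110 × 0.8), SD 1.4 ng/ml, one-sided alpha 0.0125 (0.025 / 2) and a normal approximation. The smallest observed difference that meets the rule is then 2.241 × 1.4 × √(2/88) = 0.473 ng/ml, or 39% of the planned 1.2. Any well-powered test against zero behaves this way. For HbA1c the same formula gives 2.241 × 0.3 × √(2/88) = 0.101, about half of the planned 0.2. Neither figure measures how far BDNF departs from cognition.
- **A minimum BDNF difference is missing.** The trial is designed for superiority, and testing against zero is standard for that.
- **The limitations already concede the point.** The Discussion says "we will not conduct a comprehensive investigation into motor and cognitive functions", but this concerns the depth of testing and leads to a call for neuroimaging. It neither restricts nor condemns the conclusion drawn from BDNF.

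**Conclusion.** The point holds as a mismatch between what is tested and what is declared. The rule claims a confirmed improvement in cognitive function from BDNF alone, while the outcomes by which the protocol assesses cognitive function are exploratory and play no part in the rule.

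It affects the conclusion attached to one of the two primary outcomes, in every comparison to which the rule is applied. Its numerical size is nil: the BDNF endpoint, its test, its share of alpha, its power and the planned 330 participants all stay as they are. The finding rests only on the wording of the sections cited and needs no assumption about effect size, SD or dropout. It does not predict that the cognitive tests will be null or adverse. It says only that the rule would reach the same declaration if they were.

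The wording should be changed, because it governs what the trial may report as confirmed.

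**What to change.** 1. In the Sample size calculation section, replace the BDNF sentence with: *If the lower confidence limit of the mean difference in BDNF exceeds 0 ng/ml, the intervention is declared superior for raising serum BDNF.* This also corrects the unit.
2. In the same section, align the opening hypothesis so that the confirmatory claims concern HbA1c (glucose control) and serum BDNF.
3. State in the Statistical analysis section that any conclusion on cognitive function is exploratory and is drawn only together with the reaction-time and dual-task gait results.

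The cost is a narrower headline claim. The article describes recruitment as still under way, so when it was written the change could be made before results were known.

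If the sponsor wants a confirmatory statement about cognition, a cognitive performance test would have to join the primary outcomes with its own share of alpha and its own effect size and SD. The protocol gives no such figures, so the sample size for that option cannot be worked out from it.
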